**Figure 3. f3:**
[figure not shown]
Inclusion of patients in the randomized control trial (before and after). G1, teleconsultation; G2, teleconsultation plus face-to-face consultation.

Patients in G1 and G2 will be followed up for seven and 14 days using specific instruments to assess the absence or presence of pain (Wong-Baker scale)
^
31
^ and quality of life, according to the child’s age (Child Perceptions Questionnaire, CPQ,
^
32
^ or Early Childhood Oral Health Impact Scale, ECOHIS).
^
33
^ In the case of urgencies involving teeth, a 12- and 24-month follow-up of the tooth reported in the teletriage will be carried out. The clinical criteria used to determine treatment success will be no fistula or exudate, no abscess, no painful symptoms, and no pathological mobility (
Figure 4).

**Figure 4. f4:**
[figure not shown]
The clinical criteria used to determine treatment success during patient follow-up. G1, teleconsultation; G2, teleconsultation plus face-to-face consultation.

### Inclusion and exclusion criteria

The inclusion criteria will be the same for the two stages of patient selection in the study.

*Inclusion criteria*
a)children aged 3 to 13 years, with dental pain, whose parents seek urgent care at the Dental School of the University of São Paulo in São Paulo, or at the public network in the city of Carangola, in the state of Minas Gerais.b)patients with a sufficiently good internet connection to allow a synchronous consultation.

*Exclusion criteria*

The exclusion criteria will be the same for the two stages of patient selection of the study:
a)patients who fail to attend the face-to-face consultation, when assigned to G2;b)patients with internet access difficulties.

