## Protocol

### Ethics statement

The design of this study (both before-and-after study as well as the randomized clinical trial) was approved by the Research Ethics Committee, School of Dentistry, University of São Paulo (approval no. 46974821.9.0000.0075), on June 1st, 2021. It was also submitted to
*The Brazilian Clinical Trials Registry*, code
RBR-523hrsx. The research protocol was written following SPIRIT
*(Standard Protocol Items: Recommendations for Interventional Trials)* guidelines.
^
30
^

The study will be divided into the following stages: (1) questionnaire validation, (2) randomized clinical trial, and (3) before-and-after study, each with their own methodology.

*Team and participants*

The allocation sequence was generated by an external professional (Dentist, PhD);

The participants enrollment and their assignment to interventions will be carried out by the main researcher ([name]).

*Questionnaire validation*

The inclusion of the research participants in this stage will be made upon a digital acceptance of a free and informed digital consent form (FICF), which will be digitally signed by the person in charge of the child (parents/guardians) and uploaded through a digital link, for this remote part of the study. This form presents the research objectives clearly, as well as the guidelines that will be provided to patients. Permission to disclose data will be part of this document, and shall ensure confidentiality of participant identity. All the participants will be informed that their participation in the study is voluntary and the participants will be informed that their anonymised data will be published.

*Before-and-after study nested within a randomized clinical trial*

For this stage, inclusion of participants in the study groups will also take place upon a digital acceptance of a free and informed digital consent form (FICF), uploaded through a digital link, and parents or guardians must mark the tick – box to consent for the remote part of the study, on behalf of the child. The parents/guardians of participants assigned to the face-to-face consultation group (G2) will also be required to sign a FICF.

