**Figure 2. f2:**
[figure not shown]
Validation of the questionnaire applied in the study.

*Before-and-after study nested within a randomized clinical trial*

The present research project will consist of a randomized, controlled, noninferiority, and blinded (examiners) clinical study, with 260 children aged 3 to 13 years in dental urgency situations. All of the participants investigated will be users of Basic Health Units, hospitals or dental clinics, residing in the municipality of Carangola, MG, Brazil. A link providing access to the Telehealth and Teledentistry Center from the University of São Paulo School of Dentistry (Nutes/FOUSP) platform will be sent to each patient after said patient makes the first contact through

*WhatsApp*
, a messaging app. All patients will be previously evaluated by a previously trained researcher in a teleconsultation (“before”), and then randomized and divided into two groups: G1, comprising 130 patients seen via a teleconsultation, and G2, comprising 130 patients seen via a teleconsultation and also in person (
Figure 3). The face-to-face evaluation (“after”) will be performed by two researchers who will be blinded to the result of the teleconsultation, who will perform anamnesis and clinical examination using a specific dental record, and who will answer whether or not the patient’s case is an urgent situation at the end of the evaluation. The dental condition motivating inclusion of the patient in the study will be treated by the researcher, and any other patient needs will be seen to by referring them to the health unit where they were registered.

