### Assignment

*Questionnaire validation*

The questionnaire will be applied to 140 participants, and reapplied to 14 randomized participants. Randomization, in blocks of four participants, will be performed using statistical software (MedCalc
^®^ 15.11, MedCalc Software, Ostend, Belgium), and the sequence generated will be distributed in sealed brown envelopes.

*Before-and-after study nested within a randomized clinical trial*

Randomization, in blocks of four patients, to assign them to one of the treatment groups, will be performed using statistical software (MedCalc
^®^ 15.11, MedCalc Software, Ostend, Belgium), and the sequence generated will be distributed in sealed brown envelopes. The envelopes must be opened immediately after the start of the teleconsultation.

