### Interventions

The synchronous teletriage will be carried out using the teleconsultation-dedicated
NuTes-FOUSP platform that complies with the LGPD, as well as a questionnaire containing objective questions to ascertain whether or not the situation in question is a case of a dental urgency. The time required to apply the questionnaire will depend on how long it takes to obtain the answers from the patients’ parents/guardians.

In the clinical stage of the study, the time of the face-to-face dental consultation, to be performed immediately after the synchronous consultation shall not exceed one hour.

The clinical situations listed below will be considered dental urgencies (ADA, 2020)
^
2
^:
•irreversible pulpitis;•pericoronitis;•abscess or localized bacterial infection, resulting in localized pain and swelling;•tooth fracture, resulting in pain or causing soft tissue trauma.•dental trauma, involving avulsion and/or luxation;•a missing or fractured restoration, or one causing gingival irritation and requiring a provisional restoration;•extensive caries or a defective restoration that is causing pain;•pain that requires replacing the provisional filling of an endodontic access opening;•perforated or ulcerated oral mucosa, requiring trimming or adjustment of a wire or orthodontic appliance.

The clinical situations listed below will not be considered dental urgencies:
•initial or follow-up dental examination;•routine radiography;•dental prophylaxis;•routine periodontal therapy;•orthodontic procedure other than that needed to treat an acute problem (e.g., pain, infection, trauma);•extraction of an asymptomatic tooth;•restorative dentistry procedure, including treatment of an asymptomatic carious lesion;•aesthetic dental procedure

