### Sample size

*Sample for questionnaire validation*

The guidelines of the European Statistical System stipulate that the development and validation of instruments must follow five steps: (1) conceptualization, (2) questionnaire design, (3) questionnaire testing, (4) revision, and (5) data collection.
^
34
^ Considering that the questionnaire conceptualization and design have already been completed, our considerations will begin from the questionnaire testing step. The first step involved in instrument testing is evaluation by a panel of experts (content validation). There is a controversy in the literature regarding the recommended size for this panel, ranging from five to twenty members,
^
35
^
^,^
^
36
^ depending on their experience and qualifications. Subsequently, data collection will be carried out by applying the questionnaire (criterion validity). To this end, a sample size of at least 10 participants is recommended for each item
^
37
^; therefore, the minimum sample size of the present study will be 140 subjects. In order for the instrument to be considered reliable (test and retest), it must be able to produce similar results when applied to the same individual at different times, and by different interviewers. For this purpose, a sample size corresponding to 10% of the total “N” (i.e., 14 patients in the current version of the questionnaire) should be used.

*Sample size calculation for the RCT*

Primary outcome: the presence of dental pain in children and adolescents, considering independent samples (in this case, there is no pairing of individuals, and the interventions will be assigned to different individuals). The possibility of dropouts during the follow-up period was taken into account.

In performing the sample size calculation for independent samples, the proportion of dental pain observed in children and adolescents will be considered as 32.7%,
^
38
^ and the minimum, clinically relevant proportion difference will be 15%. Thus, considering a two-tailed test, a significance level of 0.05, and a power of 0.80, the calculation will yield a total number of 236 patients. Owing to the possibility of participant dropout during the follow-up period, 10% of this number will be added to the final sample, bringing the total number of patients required per experimental group to 130 (G Power, version 3.1.9.4).

*Sample size calculation for the before-and-after study*

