### Data analysis

*Questionnaire validation*

The kappa coefficient (k) and content validity index (CVI) will be used to quantify the degree of agreement among experts during content validation. In order to assess the reliability of the instrument, the test and retest results will be evaluated using the intra-examiner agreement test (kappa test,
*k*), which is the appropriate statistical procedure to assess the reliability of categorical and nominal variables. The criterion validity will be analyzed by comparing the results of the teleconsultation with those of the face-to-face consultation using the chi-square test (χ
^2^). The significance level will be set at 5%, and the data will be analyzed using
Jamovi and
RStudio software.

*Randomized clinical trial*

Primary outcome: pain (Wong-Baker scale); secondary outcomes: quality of life (questionnaires according to age group) and missing teeth.

The primary outcome of the randomized clinical study will be any change in pain score observed at the 7-day and 14-day follow-up timepoints compared to baseline. This outcome comprises an ordinal qualitative variable; therefore, comparison between the teleconsultation and face-to-face consultation groups will be performed using the Mann-Whitney test.

Other secondary outcomes will be evaluated, such as the impact of treatments on oral health-related quality of life, and the number of missing teeth after the 24-month follow-up period. Differences between the groups regarding the final and initial scores of the questionnaires on oral health-related quality of life, as well as the number of missing teeth, will be compared using Student’s t test or the Mann-Whitney test, depending on the type of data distribution (normal or non-normal). In addition, Poisson’s regression analysis will be performed to assess the influence of other variables on the results. The significance level will be set at 5%, and the data will be analyzed using Jamovi and RStudio software.

*Before-after study nested within an RCT*

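### Exclusion criterion (a) removes children after randomisation, and only in G2, so the G1-versus-G2 comparison is no longer protected by randomisation

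*Protocol article*

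**What the plan says.** The section on inclusion and exclusion criteria lists, as exclusion (a), "patients who fail to attend the face-to-face consultation, when assigned to G2". It says that the exclusion criteria are the same for both stages of patient selection, and it does not limit (a) to the before-and-after study.

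The order of events is given in three places:

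- Research design: children are assessed by teleconsultation "and then randomized and divided into two groups: G1, comprising 130 patients seen via a teleconsultation, and G2, comprising 130 patients".
- Assignment: "The envelopes must be opened immediately after the start of the teleconsultation".
- Interventions: the face-to-face visit is "to be performed immediately after the synchronous consultation shall not exceed one hour".

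The trial is described as a "randomized, controlled, noninferiority, and blinded (examiners) clinical study, with 260 children aged 3 to 13 years". For the primary outcome, change in Wong-Baker pain score at 7 and 14 days, "comparison between the teleconsultation and face-to-face consultation groups will be performed using the Mann-Whitney test". Quality of life and the number of missing teeth at 24 months are also compared between the groups.

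The Ethics statement adds that parents of participants "assigned to the face-to-face consultation group (G2) will also be required to sign a FICF".

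**The concern.** An eligibility criterion should be decidable before allocation. This one cannot be, because it depends on what a family does once it has been assigned to G2. A G1 family that would also have missed a visit stays in the trial, while its G2 counterpart is removed. The analysed groups would then be all of G1 against the G2 children whose families attended.

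Attendance could plausibly depend on how the pain develops, on distance or on parental motivation; the article documents none of these. If attendance is related to outcome, the two groups differ for reasons other than the intervention. The comparison at stake is the trial's primary one. If excluded children are not followed, the analysis cannot repair the loss later. The Study status section says that inclusion is under way.

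**Working it through.** **Timing.** The Research design section places randomisation after the teleconsultation; the Assignment section opens the envelope just after the teleconsultation starts. The two accounts differ slightly, but on either one the face-to-face visit comes later. Missing it is therefore always a post-randomisation event, and it is possible only in G2.

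**Plan's own figures.** The article gives no attendance rate, so there is no stated figure for this point to reproduce. The dropout step does reproduce: 236 × 1.10 = 259.6, hence 260, or 130 per group. It is described as an allowance for dropout during follow-up. Extra numbers would not restore comparability in any case.

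The 236 itself does not follow from "considering a two-tailed test, a significance level of 0.05, and a power of 0.80". For 32.7% against 17.7%, the pooled formula gives [1.96·√(2·0.252·0.748) + 0.842·√(0.327·0.673 + 0.177·0.823)]² / 0.15² = 130.3, hence 131 per group and 262 in total. That is a separate matter, and nothing below depends on it.

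**Illustration of size.** Inputs: pain rate 0.327 (Sample size section), with no true difference between the arms. Assumed: a share q of G2 misses the visit, and the pain rate among those children is p. The pain rate in the G2 children who remain is (0.327 − q·p)/(1 − q).

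| q | p | Analysed G2 rate | Shift in points |
|---|---|---|---|
| 10% | 20% | (0.327 − 0.020)/0.90 = 0.341 | +1.4 |
| 10% | 10% | (0.327 − 0.010)/0.90 = 0.352 | +2.5 |
| 20% | 20% | (0.327 − 0.040)/0.80 = 0.359 | +3.2 |
| 20% | 10% | (0.327 − 0.020)/0.80 = 0.384 | +5.7 |
| any | 32.7% | 0.327 | 0 |
| 10% | 50% | (0.327 − 0.050)/0.90 = 0.308 | −1.9 |
| 20% | 50% | (0.327 − 0.100)/0.80 = 0.284 | −4.3 |

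A positive shift makes G2 look worse and so favours teleconsultation; a negative shift does the opposite. Letting p run from 0% to 70% widens the range to +3.6 to −4.1 points at q = 10%, and to +8.2 to −9.3 points at q = 20%.

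**What retention does.** A G2 child who misses the visit has had only the teleconsultation, which is G1's care. Suppose the visit makes a 15-point difference in those who attend and none in those who do not. The all-randomised difference is then 15 × (1 − q): 13.5 points at 10% non-attendance and 12.0 points at 20%. Keeping everyone removes the selection but pulls the arms together, which in a noninferiority setting leans towards the claim.

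**Before-and-after set.** With the same q, 130 × 0.90 = 117 or 130 × 0.80 = 104 children would have both examinations, unless non-attenders are replaced.

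**The case against.** The best defence is that the list is loosely drafted and that (a) was meant for the nested study. The same list is applied to the validation stage, for which no G1 or G2 is described. The before-and-after study does need both examinations. The Research design section says that patients in both groups will be followed up, without restricting this to attenders. The article is condensed, and an analysis plan that is not shown may define the analysis sets. This supports confining (a) to the nested study. It does not remove the point, because the text states an exclusion, and nothing in it keeps the excluded children in the randomised comparison. The article's silence on an intention-to-treat set is not part of the criticism.

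Three stronger readings are tempting, and the article does not support them:

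- *That the comparison is certainly biased, and in favour of teleconsultation.* There is no bias if attendance is unrelated to outcome, and the sign is unknown. A visit immediately after the call also leaves little time for pain to settle and keep a family at home.
- *That the shift uses up over a third of a noninferiority margin* (5.7/15 = 38%). The 15 points are the difference to be detected in a two-tailed calculation and are not stated as a margin. The 32.7% is a planning proportion taken from a cited source, and the primary analysis ranks changes in score. Percentage points do not carry over to it directly.
- *That the extra G2 consent form is a second one-sided exit.* The article does not say that refusal leads to removal, and the consent-flow figure is not shown.

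**Conclusion.** The point holds in a limited form. Criterion (a) as written is a one-arm, post-randomisation exclusion, and it reaches the stage that supplies the G1-versus-G2 comparison of pain, quality of life and tooth loss. This follows from the text and needs no assumption. That it would cause bias rests on one assumption: that attendance is related to outcome.

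The shift of 1.4 to 5.7 points is illustrative only. It holds for a yes/no pain outcome at 32.7%, with assumed non-attendance of 10-20% and assumed pain of 10-20% among non-attenders. Other plausible values give zero or the opposite sign. The rule should be changed because the primary comparison loses the protection of randomisation; no particular bias has been shown.

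**What to change.** - Remove (a) from the eligibility criteria of the randomised trial, and state it as a condition of the before-and-after analysis set only.
- Collect the 7- and 14-day pain and quality-of-life scores, and the later tooth outcomes, for every randomised child whether or not the visit took place. Analyse all children in the allocated group.
- Report a per-protocol analysis with equal weight, and require the two to agree before claiming noninferiority. The all-randomised analysis is exposed to dilution and the per-protocol analysis to selection, so neither is sufficient alone.
- As a precaution, and where feasible, obtain consent for a possible face-to-face visit before the envelope is opened.

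The cost is protocol wording and some extra follow-up contacts: 13 to 26 children if 10-20% of 130 do not attend. The before-and-after set falls below 130 if some G2 children do not attend and are not replaced. The protocol should say which is intended.

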### Recruitment

*Questionnaire validation stage*

The parents/guardians of children with dental pain who seek care at the University of São Paulo School of Dentistry or at the University of São Paulo Health Superintendence (SAU) will receive the contact information for one of the researchers, complete with a telephone number, and information about the requirements for having a remote consultation.

*Before-and-after study nested within a randomized clinical trial*

When arriving at a Basic Health Unit, a hospital or a dental clinic outside opening hours, the parents/guardians of children with dental pain will find a poster outside containing the contact information for one of the researchers, complete with her/his telephone number, the ethics committee approval number, and the requirements for having a remote consultation.

### Assignment

*Questionnaire validation*

The questionnaire will be applied to 140 participants, and reapplied to 14 randomized participants. Randomization, in blocks of four participants, will be performed using statistical software (MedCalc
^®^ 15.11, MedCalc Software, Ostend, Belgium), and the sequence generated will be distributed in sealed brown envelopes.

*Before-and-after study nested within a randomized clinical trial*

Randomization, in blocks of four patients, to assign them to one of the treatment groups, will be performed using statistical software (MedCalc
^®^ 15.11, MedCalc Software, Ostend, Belgium), and the sequence generated will be distributed in sealed brown envelopes. The envelopes must be opened immediately after the start of the teleconsultation.

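### Fixed, published blocks of four, with one person both enrolling and assigning, let about a third of RCT allocations be foreseen; the envelope's opening time also conflicts with the stated order of evaluation and randomisation

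*Protocol article*

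**What the plan says.** All of the following is in the protocol article.

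- **Block size.** Assignment, for the RCT stage, fixes a single size: "Randomization, in blocks of four patients, to assign them to one of the treatment groups".
- **Ratio and total.** Research design describes a "randomized, controlled, noninferiority, and blinded (examiners) clinical study, with 260 children aged 3 to 13 years", split into "G1, comprising 130 patients seen via a teleconsultation, and G2, comprising 130 patients seen via a teleconsultation and also in person".
- **Who does what.** Under Ethics statement (team and participants), an external professional generated the sequence, but "The participants enrollment and their assignment to interventions will be carried out by the main researcher".
- **Concealment.** Assignment says that "the sequence generated will be distributed in sealed brown envelopes".
- **Timing.** Assignment adds: "The envelopes must be opened immediately after the start of the teleconsultation". Research design instead has every child evaluated by teleconsultation (the before assessment) and randomised after that.
- **Entry.** Families make first contact by messaging app and are then sent the link (Research design). Eligibility includes "patients with a sufficiently good internet connection to allow a synchronous consultation".
- **Blinding.** The blinding that Research design describes is of the face-to-face evaluators, to the teleconsultation result.
- **Strata.** Data analysis, for the before-after study, labels age as a randomisation stratum. Assignment names no strata.

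**The concern.** A sealed envelope hides the next card. It does not hide what the earlier cards already imply. With blocks of one known size, someone who has seen the earlier allocations in a block always knows the fourth, and knows the third whenever the first two match. Here the person who assigns is also the person who enrols, and the groups cannot look alike to that person because one of them is sent to an in-person visit.

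If the coming group is known while there is still some latitude over whether or when a child enters, children can be steered between groups, knowingly or not. The comparisons of pain, quality of life and tooth loss would then be between groups that differed from the start.

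The timing conflict is a second route. If the envelope is opened at the start of the call, the tele decision and the baseline scores may be recorded by someone who already knows the group. That decision is the before half of the before-and-after study, and the baseline scores are the reference for the pain change that the RCT analyses.

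**Working it through.** The protocol states no predictability figure, so there is none to reproduce.

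**Inputs.** Block size 4 (Assignment); 130 v 130, hence 2 + 2 per block; 260 children (Research design). Consistency check: 260 / 4 = 65 complete blocks, and 65 × 2 = 130 per group, as stated.

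**Step 1: allocations that are certain in advance.** A block has six equally likely orders. An allocation is certain once one group's two places are used.

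| Order | Certain positions | Count |
|---|---|---|
| AABB | 3, 4 | 2 |
| ABAB | 4 | 1 |
| ABBA | 4 | 1 |
| BAAB | 4 | 1 |
| BABA | 4 | 1 |
| BBAA | 3, 4 | 2 |

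Total 8 of 6 × 4 = 24 positions, so 8/24 = 33.3%. Per block that is 4/3, and over the trial 65 × 4/3 = 86.7, about 87 of 260.

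**Step 2: best guess.** Always guess the group with more places left.

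- Position 1: 1/2
- Position 2: 2/3
- Position 3: (1/3 × 1) + (2/3 × 1/2) = 2/3
- Position 4: 1

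Sum 17/6 per block, so 17/24 = 70.8%, or 260 × 17/24 = about 184 correct, against 50% under simple randomisation.

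**Step 3: effect of changing the blocks.** The fixed sizes were enumerated. The varied sizes were simulated (300 trials of 260) with an observer who knows the set of sizes but not their order.

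| Blocks | Certain | Best guess correct |
|---|---|---|
| Fixed 4 | 33.3% | 70.8% |
| Fixed 6 | 25% | 68.3% |
| Fixed 8 | 20% | 66.6% |
| Varied 4/6 | 5.6% | 69.2% |
| Varied 4/6/8 | 2.3% | 68.0% |

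Varying the sizes nearly removes certainty but leaves guessing almost as good.

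**Step 4: illustration of a possible bias (all inputs assumed).** Suppose half of the children are severe, with day-14 pain in 45% of severe and 20% of other children. Suppose a share s of severe children is steered out of G1 in its known slots, with the mirror image in G2. The severe share in the known G1 slots is (1 − s)/(2 − s), and over all of G1 it is (2/3 × 0.5) + (1/3 × that share).

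- s = 0.25: 47.6% v 52.4%; difference 4.8 points × 0.25 = 1.2 points of pain
- s = 0.5: 44.4% v 55.6%; 11.1 × 0.25 = 2.8 points
- s = 1: 33.3% v 66.7%; 33.3 × 0.25 = 8.3 points

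The difference used in Sample size is 15 points.

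**Step 5: timing.** In Assignment the envelope is opened just after the call begins. In Research design the evaluation comes first and randomisation second. Both cannot describe the same procedure unless the evaluation is complete almost as soon as the call starts.

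**The case against.** **Safeguards and entry.** The sequence is made externally and the envelopes are sealed. Families refer themselves from a poster outside closed clinics (Recruitment), the entry criteria are few, and when the envelope is opened a working connection already exists. This limits the scope for steering and should be said. It does not close the gap. Knowledge gained by counting comes before the envelope is opened, so it is available during the earlier messaging contact, and what counts as an adequate connection is left to judgement.

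**Strata.** If age strata are used, blocks from different strata interleave, and remembering the last few allocations is not enough. This stands: one third is then the figure for someone who keeps a tally per stratum, apart from incomplete last blocks.

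**Size.** The illustration uses unadjusted pain proportions, whereas Data analysis compares change in pain score with the Mann-Whitney test, so a severity imbalance need not carry over one for one. If steering means refusal, filling the 87 known slots means turning away 87 × 0.5s/(1 − 0.5s) children: about 12, 29 or 87 for s = 0.25, 0.5 or 1. The upper end is implausible. This stands; step 4 shows a mechanism and is not an estimate.

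**Stronger readings that the document does not support.** A reader might infer that no analysis could remove the bias. Pain and quality of life are scored at baseline, the pain outcome is a change from baseline, and a regression on other variables is planned, so bias through measured severity could be reduced. Selection on unmeasured features could not. A reader might also infer that the envelopes sit with the researcher and that their opening is not independently logged. The article says neither, and a condensed article need not.

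**Conclusion.** The point holds as a weakness in procedure. With one published block size of four and a 1:1 ratio, about one third of allocations (about 87 of 260) can be known in advance, and about 71% can be guessed, by a person who keeps count. The protocol gives enrolment and assignment to the same person. The figures are exact for complete blocks. They rest on that person seeing earlier allocations, which no sentence states but which follows from doing the assigning, and on a tally per stratum if age strata are used.

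Selection bias is therefore possible, and only partly correctable through baseline pain. It would go too far to conclude that allocation has been foreseen or that any child has been steered; nothing in the document shows either.

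The conflict between Assignment and Research design over when the group becomes known is a separate matter and needs reconciling however the blocks are formed.

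**What to change.** 1. **List.** Study status says inclusion is under way, so regenerate the unused part of the sequence in permuted blocks of randomly varying size (for example 4, 6 and 8), and do not disclose the sizes to the recruiting team. State whether age strata are used, so that Assignment and Data analysis agree.
2. **Release.** Reconcile Assignment with Research design so that each assignment is released only after consent, eligibility, the tele decision and the baseline scores are recorded. The external professional who made the list, or a free web module, could do this. Release at the end of the call still precedes the in-person visit. The validation stage already makes opening the envelope depend on accepted consent or assent.

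Both parts are needed. Varied sizes deal with certainty but barely with guessing; independent release after the record is locked protects the tele decision and the baseline scores, and removes discretion over entry once the group has been revealed.

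Cost: a re-run list, a continuing small role for the list holder or a web module, and a short protocol change. Downside: a possible final imbalance of a few children between groups.
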